**Discussion:**

The results will indicate whether the proposed psychosocial intervention was effective in reducing MUVD (possibly mediated by common mental distress).

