These findings have important implications for alternative intervention strategies. Our proposed psychosocial intervention carried out in this trial (consisting of relaxing exercise and social support) aims to reduce MUVD as a result of reducing CMDs. There are only a few randomized controlled trials (RCTs) for the treatment of CMDs in the developing world [30-33]. Most of these studies have used traditional psychological models such as Cognitive Behavioural Therapy and/or Interpersonal Therapy to alleviate CMDs [34,35]. However, some studies in the West have shown the effectiveness of simpler alternative approaches such as problem solving [36,37] and group support strategies [30,38-43]. Similarly, different RCTs have demonstrated that progressive muscle relaxation and/or guided imagery can alleviate depressive symptoms by enhancing self efficacy and decreasing persistent unexplained physical symptoms [43-47].

We conducted a community-based randomized trial, comparing the experimental group (who were administered the psychosocial intervention) with the control group (who served as a treat later group). The research question is the following: **Does a community based psycho-social intervention **(combined structured social support groups and progressive relaxing exercises) alter **complaints from medically unexplained vaginal discharge **among low-income married women, aged 18-49 and residing in Hey el Sellom?

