### Instruments

The primary outcome is MUVD at six months. A woman is considered to have MUVD, if she reports a complaint of vaginal discharge as assessed by the question:" are you complaining currently from vaginal discharge?" and is concurrently not suffering from any RTIs, as confirmed by pelvic exam and laboratory tests (using swabs). Further questions were also asked of the women to note whether or not they are bothered by MUVD, as well as to indicate the colour, odour, thickness, consistency and frequency of discharge. Besides, relevant health service use such as consultations for vaginal discharge and associated treatments were also explored.

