#### Timing of assessments

Data were collected at the screening phase, at 1.5 months and at six months, with MUVD assessed at baseline and six months. CMDs were assessed at screening, at 1.5 and at six months after randomisation, and somatisation was assessed at baseline and at six months. The laboratory tests to rule out RTIs were assessed at baseline and at six months. The socio-demographic characteristics and reproductive history of the women were assessed only at baseline, while, social support factors were assessed at both baseline and at six months.

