### Analyses

The trial will be analyzed and reported in accordance with the CONSORT guidelines. An interim analysis was not planned for this trial. Descriptive statistics will be used to compare the two groups as randomized. The primary analysis will comprise the difference in the percentages of women with MUVD at 6 months between the groups as randomized (including the 95% confidence interval) and the number-needed-to-treat. Logistic regression analyses (for the primary and secondary outcomes) will be used to adjust for any baseline imbalances, and imputation methods will be used to replace missing outcome data. Clustering effects of the intervention groups will be accounted for using methods such as robust standard errors and mixed effects regression models. Potential mediators will be investigated by adding (separately) changes in HSCL-25 Anxiety and Depression sub-scales and the somatisation scale scores to the regression models with the primary outcome. Adherence to the intervention will be accounted for using instrumental variables regression models. Appropriate interaction terms will be added to the regression models for the primary and secondary outcomes to investigate differential effects of the intervention according to age and baseline HSCL-25 scores, all as continuous variables.

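### Judging mediation by adding change scores to a logistic model for MUVD can misstate it in either direction

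*Protocol article*

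**What the plan says.** The Analyses section sets out the mediation step in one sentence: "Potential mediators will be investigated by adding (separately) changes in HSCL-25 Anxiety and Depression sub-scales and the somatisation scale scores to the regression models", that is, the models for the primary outcome. Just before, it names the model type: "Logistic regression analyses (for the primary and secondary outcomes) will be used to adjust for any baseline imbalances". The primary analysis itself is on another scale, the "difference in the percentages of women with MUVD at 6 months between the groups as randomized (including the 95% confidence interval", with the number needed to treat.

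The schedule under Timing of assessments reads: "CMDs were assessed at screening, at 1.5 and at six months after randomisation, and somatisation was assessed at baseline and at six months". MUVD has two time points, "with MUVD assessed at baseline and six months". Under Instruments, the complaint is elicited as a present state: "are you complaining currently from vaginal discharge".

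Mediation is the rationale of the trial. The Background says the intervention "aims to reduce MUVD as a result of reducing CMDs", and the abstract says the results will show whether it was "effective in reducing MUVD (possibly mediated by common mental distress" (in brackets there).

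The article does not say over which interval change is taken, which covariates stay in the model, or what summary of mediation will be reported.

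**The concern.** The plan fixes an estimation approach (entering a change score in the outcome model), a scale (log-odds) and one-at-a-time entry. The natural reading of such an analysis is to compare the treatment coefficient before and after the mediator enters. Three things can distort that comparison.

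- **Non-collapsibility.** In a logistic model, adding any predictor of the outcome moves the treatment log-odds ratio away from zero, even when treatment does not affect that predictor. This works against seeing real mediation.
- **Confounding of mediator and outcome.** Women are randomised to arm, not to level of distress. A common cause of distress and discharge can look like mediation.
- **Time order.** A change measured to six months is concurrent with a complaint asked about in the present. Discharge may raise distress, rather than the reverse. For somatisation no earlier follow-up measure exists, so its change can only be concurrent.

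At stake is the explanatory conclusion, that discharge falls because distress falls. It could be wrongly dismissed or wrongly supported.

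**Working it through.** **Plan's figures.** The article gives no figure for mediation. It does give design risks of 30% vs 10% and 80-102 women per group, allowing for 10% attrition (Sample Size). With a continuity correction, the usual two-proportion formula gives 72 and 92 evaluable women per group for 80% and 90% power. Dividing by 0.9 gives 80 and 103, and 92 × 1.1 gives the stated 102. The stated range is therefore reproduced.

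Expected events in total: 72 × (0.30 + 0.10) = 28.8 and 92 × 0.40 = 36.8, so about 29 to 37, of which 7 to 9 are in the intervention arm.

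**Set-up.** Total log-odds ratio: ln[(0.1/0.9)/(0.3/0.7)] = ln(0.2593) = -1.350.

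Mediator change in SD units: M = -aT + e, with e standard normal and T = 1 for intervention. Outcome: logit P(MUVD) = c + dT + bM, with c and d solved so that the marginal risks are exactly 30% and 10%. When this model is true, the adjusted coefficient is d.

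- Apparent share = 1 - d/(-1.350).
- True share of the risk difference = (0.10 - p*)/(0.10 - 0.30), where p* is the risk under intervention with the mediator left at its control distribution.

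The values of a and b are assumptions; the article gives none.

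| Assumed a, b | d | p* | Apparent share | True share (risk difference) |
|---|---|---|---|---|
| 0, 1 | -1.546 | 0.100 | -15% | 0% |
| 0, 2 | -2.033 | 0.100 | -51% | 0% |
| 0.4, 1 | -1.146 | 0.137 | 15% | 19% |
| 0.4, 2 | -1.233 | 0.162 | 9% | 31% |
| 0.5, 1 | -1.046 | 0.148 | 23% | 24% |
| 0.5, 2 | -1.033 | 0.181 | 24% | 40% |
| 0.8, 1 | -0.746 | 0.185 | 45% | 42% |
| 0.8, 0.5 | -1.000 | 0.141 | 26% | 20% |

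Example, row 4: 1 - 1.233/1.350 = 0.087, against (0.10 - 0.162)/(-0.20) = 0.31. The true share on the log-odds scale is larger than on the risk-difference scale wherever there is mediation. In row 4 it is 41%.

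**Confounding only.** Let M have no effect on MUVD, let the arm lower M by 0.5 SD, and let an unmeasured factor drive both M and MUVD. With loadings of 0.5 on M and 1.0 on the logit, simulation gives an apparent share of about 13%. With 0.7 and 1.5 it gives about 21%. The true share is 0.

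**Reverse direction.** Let the arm lower six-month distress by 0.5 SD, let current discharge raise it by k SD, and let distress have no effect on discharge. With normal errors, the adjusted log-odds ratio is exactly -1.350 + 0.5k, so the apparent share is 0.5k/1.350:

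- k = 0.3: 0.15/1.350 = 11%
- k = 0.5: 0.25/1.350 = 19%
- k = 0.8: 0.40/1.350 = 30%

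The true share is again 0. The bias needs the arm to act on distress by its own route. If distress differs between arms only because discharge does, the formula and the simulation both give about 0%.

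**The case against.** The strongest reply is that this is a secondary, exploratory step. Mediators are only to be investigated, and the abstract says only that mediation is possible. No mediated proportion, indirect effect or test is promised. The interval and covariates are details that an article may leave to the analysis plan. The sizes above also depend on assumed effects, and the error is small in some rows (23% vs 24%, 45% vs 42%).

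Much of this stands, and it rules out several stronger readings.

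- A reader might infer that the plan ignores the 1.5-month HSCL-25. It does not say so; the interval is undefined.
- A reader might infer that no common causes will be adjusted for. The covariate set is unspecified, not empty: adjustment for baseline imbalances is planned, and socio-demographic, obstetric and social support data are collected. Adjusting for imbalance between arms does, however, serve a different purpose from controlling mediator-outcome confounding.
- A reader might infer that the plan will misstate a mediated share. It can do so, but the direction and size cannot be known from the document.

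What the reply does not remove is that the approach itself is stated, and non-collapsibility follows from the logistic scale whatever interval or covariates are chosen. The somatisation schedule is also fixed by the document.

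A fair warning concerns the remedy. With 29 to 37 events, a model with arm, mediator, their interaction and four covariates would have only about 4 to 5 events per parameter.

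**Conclusion.** The concern holds in this form: the before/after change in the treatment log-odds ratio is not a reliable guide to mediation here, and it can err in either direction. At 30% vs 10% it gives about -15% to -51% with no mediation, 9% to 15% against a true 19% to 31% when the arm shifts the mediator by 0.4 SD, about 13% to 21% from confounding alone, and 11% to 30% when distress responds to discharge and not the reverse. In some moderate scenarios it is nearly right on the risk-difference scale.

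These figures rest on assumed mediator strengths and arm effects, a normally distributed mediator, and reading mediation from the shift in the coefficient. They show what can happen; they do not predict this trial's result. A reader might also infer that the trial's main result is at risk. It is not: the primary comparison of percentages as randomised does not use the mediators. The change is worth making because mediation is the trial's stated mechanism and a better estimator needs no new data.

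**What to change.** Before the mediation analysis is run, amend its wording as follows.

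1. Take the change in HSCL-25 from baseline to 1.5 months as the main mediator, with anxiety and depression entered separately as planned. It falls at about the end of the six-week programme and precedes the outcome.
2. Estimate direct and indirect effects as risk differences, the scale of the primary analysis, by model-based standardisation. Do not interpret the shift in the log-odds ratio as a mediated share.
3. Adjust for baseline HSCL-25 and a small set of baseline covariates already collected, chosen as likely common causes of distress and discharge. Keep the treatment-by-mediator interaction for a sensitivity analysis, because events are few.
4. For intervals, resample therapy groups in the intervention arm and individual women in the control arm, where no groups are described.
5. Add a sensitivity analysis for unmeasured mediator-outcome confounding. An earlier mediator does not remove that problem.
6. Label the somatisation change, and any six-month HSCL-25 change, as concurrent and exploratory.

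The cost is analysis-plan wording and standard software. There are two downsides: a 1.5-month mediator misses later changes in distress before the six-month outcome, and precision will be limited, so the indirect effect should be reported with its interval and without a confirmatory claim.

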From a woman's perspective, the subjective burden of self-perceived illness and abnormality can be as important as a result of disease due to a biomedical confirmed condition. For example, in Muslim communities, vaginal discharge is considered troublesome because it affects the woman's prayer requirements to be "clean" [7]. Self-perceived illness and abnormality also affect health-seeking behaviour, leading often to unnecessary spending on health care and ineffective management [8,9]. In fact, the syndromic management of vaginal discharge can lead to inappropriate treatment of a large proportion of women, as well as unnecessary spending on treatment of non-existing RTIs [8,13].

An alternative explanation to MUVD has been recently suggested. Several observational studies confirmed the contribution of anxiety and depression to medically unexplained gynaecological symptoms, such as pelvic pain and abnormal vaginal discharge [5,12,14-22]. Taking the already discussed UHS, the sub-sample analysis pertaining to Hey el Selloum sample, showed that a large proportion of women (42%) reported mental distress- as assessed by GHQ-12. Moreover, multivariate analysis showed that mental distress was significantly associated with reported abnormal vaginal discharge, after adjusting for relevant risk factors and reported RTIs [23]. Women considered stress to be a main cause of their discharge [24] and identified mental as well as psychological health as important elements contributing to their perception of good reproductive health [4]. The UHS also showed that both mental distress and reported gynaecological health problems were negatively associated with social support [25].

Along the same line, population-based studies from South Asia show significant associations between complaints of vaginal discharge and psychosocial stress, in addition to psychosomatic symptoms such as dizziness, backache, and weakness [12,14,26]. Qualitative studies in India indicated that women typically associate complaints of discharge with mental stress and related symptoms such as tiredness [12]. On the other hand, social support is consistently associated with common mental disorders (CMD) and physical conditions [27]. Improvements in social support were shown to lead to lower consultation rates [27,28] and reduced sickness absences [29].

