### Sample Size

The sample size calculation was based on the primary outcome of reported MUVD at six months. Allowing for 10% attrition, a sample size of 80-102 in each group would provide 80-90% power to detect a difference of 20 percentage points (for example, 10% vs. 30%) in the proportion reporting MUVD at 6 months, using a 2-sided 5% significance level. There is no previous study that can directly inform the effect size likely for this outcome, but studies have found differences in recovery rates for CMD of up to 40% between usual care and active interventions for common mental disorders (4, 10, 11). We have opted for a 20 percentage point difference given these previous studies on CMD and our judgement that this is both a clinically significant and plausible difference in MUVD rates.

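### Social support is delivered by the intervention and measured twice, but no stated inferential analysis uses it, leaving the planned distress-mediation estimate open to confounding by support

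*Protocol article*

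**What the plan says.** The research question in the protocol article's Background describes the intervention as "combined structured social support groups and progressive relaxing exercises". The Intervention section gives the group discussions 75 minutes and the relaxation exercises 30 minutes, each twice a week for six weeks.

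The Background reports from the earlier household survey that "both mental distress and reported gynaecological health problems were negatively associated with social support". The trial takes its support questions from that survey. They appear under Other measures/cofactors; the secondary outcomes listed are HSCL-25 common mental disorder and somatisation.

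Timing of assessments confines socio-demographic and reproductive history to baseline, but states that "social support factors were assessed at both baseline and at six months". MUVD is also assessed at those two times. HSCL-25 has an additional assessment at 1.5 months.

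On mediation, the Analyses section says: "Potential mediators will be investigated by adding (separately) changes in HSCL-25 Anxiety and Depression sub-scales and the somatisation scale scores" to the regression models for the primary outcome. It also provides for logistic adjustment for baseline imbalances, descriptive comparison of the groups, and instrumental-variable models for adherence. The Abstract's Discussion raises mediation by common mental distress as part of what the results may show.

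**The concern.** Two things follow from this design.

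First, the six-month support measure has no stated inferential use. A variable needed only for baseline adjustment would not have to be measured again, so the repeat suggests that change was of interest. Without a between-arm estimate, a null MUVD result would be harder to read: the stated analyses would not help to separate support that did not rise from support that rose without reducing complaints.

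Second, the mediator models estimate the association between change in distress and MUVD given treatment arm. Randomisation protects the comparison of arms. It does not protect the distress-MUVD association within arms. A variable related to both can confound that association even when it is perfectly balanced between arms, so the provision to adjust for baseline imbalances does not answer the point. The protocol itself supplies such a variable: support was related to both distress and gynaecological complaints in its own survey.

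At stake is the explanatory conclusion about distress as the route of effect. The MUVD comparison at six months is not at stake.

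**Working it through.** **1. The plan's own sample size.** Inputs from Sample Size: 10% v 30% MUVD, "using a 2-sided 5% significance level", "Allowing for 10% attrition", and "a sample size of 80-102 in each group would provide 80-90% power to detect a difference of 20 percentage points".

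- Formula: n = [1.96·√(2·0.2·0.8) + z·√(0.1·0.9 + 0.3·0.7)]² / 0.2², then the continuity correction n' = (n/4)·[1 + √(1 + 4/(0.2n))]².
- 80% power: n = 62 uncorrected, 72 corrected; 72/0.9 = 80.
- 90% power: n = 82 uncorrected, 92 corrected; 92/0.9 gives 103, and 92 × 1.1 gives 102.

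The stated 80-102 is reproduced with the continuity correction, so 72-92 evaluable women per arm is the right basis for what follows.

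**2. Expected MUVD events.** 72 × (0.10 + 0.30) = 28.8 and 92 × (0.10 + 0.30) = 36.8, that is, about 29-37 in total. This limits how many terms a mediator model can carry.

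**3. How distress can be credited with an effect that ran through support.** Every value here is assumed. Let treatment T (0/1) raise support S by *a* SD. Let distress D have within-arm correlation −ρ with S, both with within-arm SD 1. Let MUVD risk fall by *c* per unit of S, with no effect of D itself (linear scale).

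- Total treatment effect: −ca.
- Within arm, the slope of S on D is −ρ. A model with T and D only therefore gives D the coefficient (−c)(−ρ) = cρ, although its true effect is zero.
- The arms differ in D by −ρa, so the treatment coefficient becomes −ca − (cρ)(−ρa) = −ca(1 − ρ²).
- Apparent share mediated by distress: 1 − (1 − ρ²) = ρ². The true share is 0.

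| ρ | ρ² | Simulated share (200,000 women, a = 0.5) | D coefficient without S | D coefficient with S |
|---|---|---|---|---|
| 0.3 | 0.09 | 0.088 | 0.044 | 0.000 |
| 0.5 | 0.25 | 0.245 | 0.072 | 0.001 |
| 0.7 | 0.49 | 0.502 | 0.102 | −0.001 |

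A second set of assumptions used logistic models with a control rate of about 30%, support raised by 0.5-0.8 units, distress lowered by 0.3-0.7 per unit of support, and log-odds of MUVD lowered by 0.5-1.0 per unit of support. It gave an apparent share of 4-22% and a spurious odds ratio of 1.14-1.55 per unit of distress, which returned to about 1.0 once support was added. The mechanism is the same in both; the size depends on the inputs.

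**4. Size against sampling error.** A similar logistic set-up at 72-92 women per arm, with an assumed direct treatment log-odds effect of −0.5, gave median apparent shares of about 1-15%. The 95% sampling ranges ran from −21% to 44% (weakest effects, n = 72) and from 2% to 59% (strongest, n = 92). In one trial of this size the bias would be hard to tell from noise.

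**5. Would a between-arm comparison of support be informative?** Detectable difference at 80% power = 2.80·√[2(1 − r²)/n] in SD units, where r is the assumed correlation between baseline and six months.

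- r = 0: 2.80·√(2/72) = 0.47 and 2.80·√(2/92) = 0.41.
- r = 0.5: 2.80·√(1.5/72) = 0.40 and 2.80·√(1.5/92) = 0.36.

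These figures are before any allowance for clustering by intervention group; the documents give neither group size nor intraclass correlation.

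**The case against.** The strongest reply is that the plan tests the theory it states. The Background says that the intervention is meant to reduce MUVD by reducing common mental disorder, and the mediators match that. If support works by lowering distress, it lies upstream on the same path, and crediting distress is correct. The survey reports associations only, and the calculations above assume the opposite of the trial's hypothesis. The article is also condensed, and a full analysis plan may say more.

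Much of this stands, and it rules out several stronger readings that a reader might infer:

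- *That the trial cannot show whether support rose.* The data are collected; only the stated analysis is lacking.
- *That the mediator list is closed, or that support is never compared between arms.* The Analyses section names mediators without excluding others, and its descriptive comparison of the groups is not limited to particular variables or times.
- *That the trial fails to test its main component.* Discussion takes 75/105 = 71% of the scheduled contact minutes, but it is given with relaxation as one package, so no analysis of the support score isolates it. The Intervention section names empathy, venting and problem solving as the aims of the sessions; general survey questions may miss these, so an unchanged score would not cleanly show failed delivery.
- *That delivery goes unexamined.* Attendance and a technique checklist are recorded, and adherence is modelled.
- *That distress will be wrongly credited.* This happens only if support affects MUVD other than through distress.

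What survives is narrower. The article does state the mediator models, and none is said to hold support constant. A route outside distress is not fanciful on the protocol's own account: the Background links support to physical conditions as well as to mental disorders.

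**Conclusion.** The point holds in limited form. As written, the plan does not formally test whether social support rose, and its distress-mediation estimate can be confounded by a variable that the protocol itself ties to both distress and gynaecological complaints. The bias is conditional on support affecting MUVD by some route other than distress. Its size cannot be stated: the shares of 4-22% and about 9-50% come from assumed effects, with distress given none of its own, and show only that the mechanism works. At 72-92 women per arm, sampling error in the mediated share is as large or larger.

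The primary MUVD comparison and its number needed to treat are unaffected. The matter is confined to explanatory analyses, but mediation by distress is part of what the trial hopes to report, and the remedy is cheap.

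**What to change.** In the Analyses section:

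1. Include baseline social support as a covariate in every mediator model, whether or not the arms are balanced on it.
2. Report the baseline-adjusted between-arm difference in six-month social support, with its confidence interval and allowing for clustering by intervention group, as an explanatory process outcome.
3. As an exploratory sensitivity analysis only, report the HSCL-25 mediator models with and without change in social support. If support acts wholly through distress, the distress coefficient should barely move; if it moves clearly, distress alone does not account for the association. State that support and MUVD are both measured at six months, so temporal order is not established and distress could itself alter reported support. State also that only about 29-37 MUVD events are expected at 10% v 30%.

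The cost is a few sentences and a few model fits on data already collected, one more secondary comparison, and slightly less precise mediator models. Specifying this before the results are known avoids its looking post hoc. It will not isolate the support component from the relaxation component, and the report should say that the support questions may not capture all that the sessions aimed at.
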